### Implementation of Family Spirit Nurture

It is widely recognized that intervention during the first 1000 days is an important strategy for reducing risk for obesity and obesity-related morbidities over the life course [49–51]. A recent systematic review identified several risk factors during the first 1000 days that are associated with later childhood overweight, including excess maternal weight gain during pregnancy, higher maternal pre-pregnancy body mass index (BMI), gestational diabetes, low socioeconomic status (SES), high infant birth weight, and rapid infant weight gain in the first 6 and 12 months of life [39]. Another systematic review found that even the existing childhood obesity research studies beginning in pregnancy do not extend beyond the first months of life. Authors of this review urge researchers to examine outcomes until at least two years postpartum [52].

This study will assess the impact of a home-visiting program, called Family Spirit Nurture (FSN), on reducing early childhood obesity in NA children during this critical developmental time period, from pregnancy to age 2, with potential to impact obesity and obesity-related morbidities over the life course. The FSN intervention is delivered from pregnancy until 18 months postpartum (with follow-up through 24 months postpartum) and is built on a strong platform: the evidence-based Family Spirit (FS) home-visiting program model, designed and evaluated by the Johns Hopkins Center for American Indian Health (JHCAIH) with tribal communities over a 20-year period [53, 54]. Over 120 tribal communities and 2 non-Native communities across 20 states have been trained to deliver the FS model. The current study integrates new curriculum content and activities into FS that are directed at obesity prevention. In addition, this study examines how the home-visiting behavior change intervention impacts underlying metabolic health through collection of maternal and infant blood samples.

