### Randomization

Participants are individually-randomized to receive the intervention or control program. Randomization is completed after the completion of the baseline assessment. Randomization is stratified by age (< 18 years old and 18 years and older), site, and food and water security status. Randomization lists for each site were created and uploaded to REDCap prior to study initiation using STATA 14 statistical software [61]. The randomization lists are not accessible by study staff. After baseline is complete, the field coordinator verifies baseline data and randomizes the participant in REDCap. Study staff are then informed of the participant’s study allocation. This is locked and unchangeable within REDCap.

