### Data collection time points

Our mixed-methods assessment includes maternal self-reports and interviews administered using Research Electronic Data Capture (REDCap) tools hosted at Johns Hopkins University, observations (including maternal/infant anthropometric measurements, infant accelerometry, and home safety assessments), maternal/infant medical chart reviews and maternal/infant blood sample collection (Table 2). REDCap is a secure, HIPAA compliant, web-based application designed to support data capture for research studies. It provides 1) an intuitive interface for validated entry; 2) audit trails for tracking data manipulation and export procedures; 3) automated export procedures for seamless data downloads to common statistical packages; and 4) procedures for importing data from external sources [68].

**Table 2 Tab2:** List of Evaluation Measures

		Pregnancy		Postpartum							
		Baseline	36 weeks gestation	2 weeks post-partum (pp)	2* months pp	4 months pp	6* months pp	9 months pp	12* months pp	18* months pp	24* months pp
Self-Report Interviews											
1. Maternal Demographics	15 min	X	X	X	X		X		X		X
2. Child Feeding Assessment [70]	10–20 min			X	X	X	X	X	X	X	X
3. Maternal Beverage Intake Questionnaire [70]	5 min	X	X		X		X		X	X	X
4. U.S. Household Food Security Survey [71]	3–10 min	X			X		X		X	X	X
5. Brief Infant Sleep Questionnaire (BISQ) [72]	5 min				X		X		X	X	X
Self-Reports											
6. Current Eating Environment Assessment	5 min				X		X		X		X
7. Infant Responsive Feeding Scale [73]	5 min				X		X		X		
8. Toddler Responsive Feeding Scale [73]	5 min										X
9. Baby Eating Behavior Questionnaire [74]	5 min						X				
10. Children’s Eating Behavior Questionnaire – Toddler [75]	5 min								X		
11. Perceptions of Growth Scale [76]	3 min				X		X		X		X
12. Child Physical Activity Assessment	5 min				X	X	X	X	X	X	X
13. Knowledge Questionnaire - Maternal Nutrition, Feeding and Physical Activity Practices	10 min	X			X		X		X	X	X
14. Water Availability Assessment [77]	5 min	X			X		X		X		X
15. Perceived Stress Scale [78, 79]	3 min	X			X		X		X	X	X
16. Centers for Epidemiologic Studies Depression Scale-Revised (CESDR-10) [80]	5 min	X	X	X	X		X		X	X	X
17. Alcohol, Smoking and Substance Involvement Screening Test (ASSIST) [81, 82]	5 min	X							X		X
18. Mastery Scale [83, 84]	5 min	X			X		X		X		X
19. Infant Temperament [76]	3 min				X	X	X	X			
20. Brief Infant Toddler Social Emotional Assessment (BITSEA) [85]	10 min								X	X	X

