21. Participant Satisfaction Questionnaire	10 min									X	
22. Injury Assessment	10 min	X							X	X	X
Observations Completed by Study Staff											
23. Toddler Physical Activity Assessment (Accelerometer) [48]	10 min									X	X
24. Maternal Height and Weight	5 min	X			X*				X*		X
25. Child Weight and Length	5 min			X	X	X	X	X	X	X	X
26. Home Safety Environment Scan	5–30 min		X	X				X	X		X
Specimen Collection											
27. Blood Sample Collection – Mothers	5 min			X (delivery)			X				
28. Blood Sample Collection – Infants	5 min			X (delivery)			X		X		
Process Form Completed by Study Staff											
29. Session Summary Form	No participant time burden	ADMINISTERED AT ALL VISITS									
Medical Chart Reviews											
30. Maternal Medical Chart Review	No participant time burden	THROUGHOUT THE STUDY PERIOD									
31. Child Medical Chart Review											
Total Participant Time Burden** (min):		58 min	30 min	75 min	104 min	28 min	114 min	43 min	151 min	98 min	151 min

**Maternal weight only will be collected at these time points*

***The 2-month, 6-month, 12-month, 18-month and 24-month assessments are completed in two sittings, to reduce participant burden. The interviews and observations are completed in the first sitting, and the self-report assessments are completed one week later*

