#### Primary aims analysis

We will conduct intent-to-treat analyses to estimate effects of the FSN + OSC intervention compared to the OSC + IPE control condition on early childhood obesity and related risk factors. Separately, we will examine the effects of intervention dose and conduct a “completer analyses” on subjects receiving minimum intervention dose (> 50% of lessons). Analyses will be adjusted for multiple comparisons using Bonferonni corrections.

Demographic and outcome variable distributions will be examined to assess whether comparability between intervention groups at baseline was achieved through randomization. For time discrete outcome measures, t- tests or chi-square tests will be used to test whether the intervention impacted each outcome in unadjusted analyses. Multiple linear or logistic regression will be used to test the impact of the intervention on each outcome, controlling for baseline demographic characteristics where necessary and examining potential moderators in secondary analyses. For time varying outcome measures we will examine the impact of the intervention by analyzing between group differences at each time point using t-tests and multiple regression analyses. For those outcomes with sufficient power, multi-level mixed-effects regression with a random effect at the individual level and appropriate variance structures, and an interaction term for treatment x child age will be used to examine change over the course of the intervention period for the intervention and control groups.

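### Primary-model covariates are demographics only, added 'where necessary' with no criterion; stratification factors and prognostic baseline measures are not named, and no estimate is named as primary

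*Protocol article*

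**What the plan says.** All references are to the protocol article.

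- **Primary aims analysis**, baseline check: "Demographic and outcome variable distributions will be examined to assess whether comparability between intervention groups at baseline was achieved through randomization". No threshold or consequence is attached to it.
- **Primary aims analysis**, outcomes measured once: t-tests or chi-square tests unadjusted, then linear or logistic regression "controlling for baseline demographic characteristics where necessary and examining potential moderators in secondary analyses". Both are described as testing the intervention's effect, and neither is called primary.
- **Primary aims analysis**, time-varying outcomes: "analyzing between group differences at each time point using t-tests and multiple regression analyses", followed by mixed models for outcomes with enough power. No covariates are named.
- **Randomization**: "Randomization is stratified by age (< 18 years old and 18 years and older), site, and food and water security status". These factors do not reappear in the primary analysis. The same section says "Randomization is completed after the completion of the baseline assessment", so baseline measures are legitimate covariates.
- **Table 2**: the baseline visit includes the "Maternal Beverage Intake Questionnaire", a knowledge questionnaire on nutrition, feeding and physical activity, and "Maternal Height and Weight". The number of previous children is known from eligibility (**Recruitment**).
- **Implementation of Family Spirit Nurture**: among risk factors for later childhood overweight the article lists "higher maternal pre-pregnancy body mass index (BMI").

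**The concern.** The child outcomes cannot have a pre-randomisation value, so any precision gained from covariates must come from maternal and household baseline data. The plan confines adjustment to demographics and makes it conditional. If the condition is observed imbalance, the criterion is a poor one: a variable that differs between arms by chance need not predict the outcome, and a variable that does predict it is worth including even when the arms are balanced.

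Three things are at stake.

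1. Precision in a trial whose stated detectable differences leave no slack.
2. Discretion. Covariates may be chosen after the arms have been compared, and an unadjusted and an adjusted result may differ with nothing to say which one counts.
3. Agreement between design and analysis. Randomisation was stratified, but the stratification factors are not in the stated models. Leaving out strata that predict the outcome generally makes the standard error too large.

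**Working it through.** **Inputs from the article.** 338 mothers, 169 per arm; 16% loss by 24 months; 80% power; 5% significance (two-sided assumed); detectable BMI z-score difference 0.33 SD (Sample size section and Table 3).

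**Input not in the article.** R², the share of outcome variance explained by the baseline covariates. I take 0.04 to 0.16, which corresponds to a correlation of 0.2 to 0.4 between maternal BMI and BMI z-score at 24 months.

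**1. Reproduce the stated figure without covariates.**
- Evaluable per arm: 169 × 0.84 = 141.96, about 142.
- Detectable difference: (1.960 + 0.842) × √(2/142) = 2.8016 × 0.1187 = 0.332 SD.
- Power at exactly 0.33 SD is 79.4% (normal approximation).

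The stated 0.33 SD reproduces with no adjustment. The article obtained it by simulation, so this is a consistency check.

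**2. Add fixed adjustment.** The residual SD becomes √(1 − R²), so the detectable difference is 0.3325 × √(1 − R²). Power is from the noncentral t at 0.333 SD with 142 per arm. The equivalent gain in sample size is 1/(1 − R²) − 1.

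| Assumed R² | Detectable difference (SD) | Power at 0.333 SD | Equivalent extra sample |
|---|---|---|---|
| 0 | 0.332 | 79.9% | – |
| 0.04 | 0.326 | 81.4% | 4% |
| 0.16 | 0.305 | 86.2% | 19% |

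**3. Does adjusting only on imbalance recover the gain?** Simulation: 10,000 runs, 142 per arm, one continuous covariate. In the third strategy the covariate enters only if its baseline t-test gives p < 0.05; that threshold is an assumption, since the article gives none. The power columns use an effect of 0.33 SD.

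| Assumed R² | Never adjust | Always adjust | Only if imbalanced | Type I error, only if imbalanced |
|---|---|---|---|---|
| 0.05 | 79.45% | 81.47% | 79.68% | 5.11% |
| 0.10 | 78.93% | 82.86% | 79.26% | 4.71% |
| 0.20 | 80.48% | 87.74% | 81.12% | 4.30% |

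At R² = 0.10 the conditional rule gains 0.33 points and the fixed rule 3.93. At R² = 0.20 the gains are 0.64 and 7.26 points. The conditional rule keeps almost none of the benefit, and its type I error stays close to 5%.

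**The case against.** **Detail belongs in the analysis plan.** A journal article need not list covariates, and a plan not shown may do so. That stands for the list itself. It does not excuse the rule the article does state. A later plan either follows that rule and inherits its weakness, or contradicts it.

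**The imbalance trigger is not written down.** True. The article never defines necessity, and a sentence on unadjusted tests separates the comparability check from the covariate clause. The trigger is an inference, but on any reading the choice is left open.

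**The clause may not govern BMI z-score.** It closes the description of outcomes measured once. BMI z-score is defined over time in the Outcomes section but powered at 24 months, so its class is arguable. If it is time-varying, the text names no covariates at all, which leaves the choice just as open.

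**Stronger readings that a reader might infer, and that the article does not support:**
- *That the trial ignores its strongest predictors.* The article gives no prognostic strengths. It names pre-pregnancy BMI as a risk factor, but says nothing comparable for maternal beverage intake, knowledge score or parity. These are plausible candidates only, and parity might already count as demographic.
- *That these data go unused.* Pre-pregnancy BMI appears as a possible moderator or mediator of infant metabolic health (Secondary outcomes), and maternal characteristics enter the biomarker models (Secondary aims analysis). They are missing only from the stated primary treatment-effect models.
- *That pre-pregnancy BMI is a ready baseline measure.* Table 2's baseline weight is taken during pregnancy. Pre-pregnancy BMI would have to come from chart review, which is completed after 24 months and whose completeness is unknown.
- *That the results would be biased or the sample size is wrong.* The simulation shows no inflation of type I error, and the stated figure reproduces unadjusted.

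**Conclusion.** The point holds as a weakness in a stated rule, not as an error. The primary regression is tied to demographics under an undefined condition, the stratification factors and other pre-randomisation prognostic measures are not named, and no estimate is designated primary. The harm is lost precision and analyst discretion.

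The size is illustrative. It applies to BMI z-score alone and rests on an assumed R²: a gain of 1.5 power points at 0.04 (81.4 − 79.9) and 6.3 at 0.16 (86.2 − 79.9). The low end is modest. No gain has been calculated for the other outcomes. Three of the six powered outcomes are binary and would use logistic regression, to which the √(1 − R²) formula does not apply.

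**What to change.** Replace the conditional wording with a short covariate list per outcome, fixed before unblinded analysis and applied whatever the observed balance:

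- **All outcomes:** the stratification factors (age group, site, food and water security status).
- **BMI z-score:** also parity and maternal BMI. Use pre-pregnancy BMI from the chart if available, otherwise baseline height and weight together with gestational age at measurement, because that weight includes gain to date.
- **SSB outcomes:** also baseline maternal beverage intake.
- **Breastfeeding and feeding-style outcomes:** also parity and baseline knowledge score.

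Name the adjusted estimate as primary and the unadjusted one as supportive. Keep the baseline comparison descriptive, with no role in choosing covariates. Exclude anything arising after randomisation, such as birth weight or total gestational weight gain.

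**Cost:** wording only, since the measures are already collected or, for pre-pregnancy BMI, depend on the planned chart review. Missing baseline values need a simple stated rule, and the choice between chart BMI and measured BMI should be made on completeness before the arms are compared. For logistic models, the plan should say that the adjusted odds ratio is conditional on the listed covariates.

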#### Secondary aims analysis – Biologic measures

Descriptive analyses, followed by Pearson’s pairwise correlation analyses will be conducted to examine maternal/infant correlations separately at delivery, 6 and 12 months for each biomarker (fasting glucose, insulin, leptin, adiponectin, lipids, and C-reactive protein). The ratio of maternal/infant biometrics and infant biologic metrics alone will be examined by time point and stratified to examine whether there are differences by maternal baseline characteristics (delivery, 6 and 12 months) and/or maternal/infant behaviors (6 and 12 months only). Infant multiple regression predictive models will be developed for each biologic outcome separately at delivery, 6 and 12 months to determine which maternal characteristics and/or behaviors (6 and 12 months only) are predictive of infant biomarker levels at each time point. Mixed effects models with a random effect at the family level will be used to adjust for mother/infant clusters. Mixed effects models adjusted for repeated measures, with appropriate correlation structures and a random effect at the family level will be used to examine how the maternal/infant ratio of each biomarker as well as infant biomarkers alone change between delivery, 6 and 12 months postpartum. Multiple regression predictive models will be developed for each biologic outcome to examine whether changes between delivery, 6 and 12 months differ by maternal characteristics and/or maternal/infant behaviors. Interaction terms between covariates and infant age will be included where appropriate. All models will be controlled for study group (intervention begins before delivery). Finally, infant biologic outcomes will be compared by study group at 6 and 12 months postpartum using t-tests. Multiple linear regression will be used to control for confounders/effect modifiers. Analyses will also be conducted at 12 months postpartum to determine whether the impact of the intervention on behavioral or physiologic outcomes was moderated by infant metabolic health at delivery, using multiple linear or logistic regression as appropriate. An interaction term between study group and each biologic outcome will be included in separate models.

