### Recruitment

The study is recruiting *N* = 338 expectant NA mothers who: 1) are between the ages of 14 and 24 at conception, 2) are less than 32 weeks gestation at consent, 3) have one or no other children, and 4) live within 50 miles of the Indian Health Service (IHS) medical facility in each participating community. Participants must be willing to undergo random assignment and participate in all aspects of the study. All participants must complete informed consent to participate. Participants under age 18 must have parent/guardian consent. The first participant was consented on October 16, 2017, and the first randomization occurred on December 1, 2017.

We are using non-probability sampling to recruit participants. Through an approved waiver of HIPAA Authorization, study staff obtain demographic information from potential participants’ electronic health records and clinic visit appointment logs at participating health clinics. This allows them to directly contact potentially eligible participants. Participants are recruited through local health and social service agencies (i.e., OB/GYN clinics, WIC programs, etc.), through public postings in community gathering spots (i.e., grocery stores, clinics, WIC offices, schools, etc.), through public service announcements on the local radio, and by print advertising in the local newspaper. Participants are also recruited during public gatherings (i.e., health fairs, job fairs, etc.). We are recruiting participants over a 24-month period (Fall 2017-Fall 2019).

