#### Lesson frequency and duration

FSN consists of 36 comprehensive lessons delivered bi-weekly from 28 weeks gestation until birth, weekly from birth to 3 months postpartum, bi-weekly from 3 to 6 months postpartum, and monthly from 6 to 18 months postpartum. Each visit is expected to take up to 60 min. Dosage is based on past evidence that effective home-visiting programs have generally planned for ~ 60 visits over a 1- to 5-year period and aimed to deliver between 32 and 56% of these visits (range 22–33 visits) [67]. Past Family Spirit trials established feasibility of proposed schedule [63].

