
#### Secondary outcomes

Group differences in levels of maternal stress over time as assessed by the Perceived Stress Scale 4 (PSS-4). Completed by mothers from pregnancy to 24 months pp., the 4-item questionnaire assesses maternal stress. It is scored with a five-point Likert scale. The range of the five-point Likert scale is as follows: 0 (never), 1 (almost never), 2 (sometimes), 3 (fairly often), 4 (very often). We will reverse scores for items 2 and 3. On these questions, the scores will be as follows: 4 (never), 3 (almost never), 2 (sometimes), 1 (fairly often), 0 (very often). Scores for each item will be summed to get a total score. The lowest score is 0 and the highest score is 16. Higher scores are correlated to more stress (worse outcome).Group differences in depression scores over time (pregnancy to 24 months pp) as assessed by the Centers for Epidemiological Studies Depression Scale-Revised-10 (CESDR-10). The 10-item questionnaire is a validated adapted version of the CESD-R (which has been utilized to assess depression with Navajo mothers) to screen for depression in adolescents. The questionnaire asks participants to rate how often over the past two weeks have they experienced symptoms associated with depression, such as restless sleep, poor appetite, and feeling sad. Response options range from 0 to 4 for each item, with 0 = *not at all or less than 1 day in the last 2 weeks*, 1 = *1–2 Days*, 2 = *3–4 Days*, 3 = *5–7 Days*, 4 = *Nearly every day for 2 weeks*. Scores for each item will be summed to get a total score. Scores range from 0 to 40, with high scores indicating greater depressive symptoms (worse outcome). A CESD-R score of 8 or greater indicatesGroup differences in alcohol and drug use over time (pregnancy to 24 months pp) as assessed by the Alcohol, Smoking and Substance Involvement Screening Test (ASSIST). Adapted from the WHO ASSIST questionnaire covering 10 main substance groups, this 15-item questionnaire screens for all levels of problem or risky substance use (alcohol, illegal drugs, and prescription drugs). A risk score is provided for each substance, and scores are grouped into low, moderate, or high risk. Only items 2–7 and 9–14 are scored. Each of these questions has a set of responses to choose from, and each response has a numerical score. The scores from questions 2–7 are added together, and the scores from questions 9–14 are added together to produce an ASSIST risk score for each substance that falls into one of three categories: low, moderate, or high substance-related risk. Participants with risk scores 3 or less (10 or less for alcohol) are at lower risk of problems related to their substance use. Participants scoring between 4 and 26 (11 and 26 for alcohol) are at moderate risk of health and other problems and may be experiencing some of these problems right now. A score of 27 or higher for any substance suggests that the participant is at high risk of dependence or is dependent on that substance and is probably experiencing health, social, financial, legal, and relationship problems as a result of their substance use.Group differences in how infant biologic measures of metabolic health (fasting glucose, insulin, leptin, adiponectin, lipids panels, and c-reactive protein) at delivery and 6 months postpartum correlate to maternal biologic measures of metabolic health. Blood specimens are collected from mothers at delivery and 6 months postpartum. Blood specimens are collected from infants at delivery (cord blood), 6 and 12 months postpartum. Laboratory testing will be completed to assess levels of fasting glucose, insulin, leptin, adiponectin, lipids panels, and c-reactive protein in mothers and babies to examine how infant metabolic health relates to maternal metabolic health at delivery, and whether there are between group differences in this relationship over time. In all cases, higher levels indicate poorer metabolic health.Group differences in infant metabolic health at delivery, 6 and 12 months postpartum. Blood specimens are collected from infants at delivery (cord blood), 6 and 12 months postpartum. Laboratory testing will be completed to assess levels of fasting glucose, insulin, leptin, adiponectin, lipids panels, and c-reactive protein in infants to examine whether there are between group differences in infant metabolic health at delivery and over time (delivery to 12 months postpartum). In all cases, higher levels indicate poorer metabolic health. In addition, results will be used to determine whether infants are insulin resistant and/or leptin insensitive (these will be dichotomous outcomes) and between group differences will be assessed at delivery and over time (delivery to 12 months postpartum).Examination of whether group differences in infant metabolic health at delivery, 6 and 12 months postpartum are moderated or mediated by sociodemographic, biological (e.g. pre-pregnancy BMI, gestational weight gain, gestational diabetes, etc.), and psychosocial characteristics of mothers at baseline). Blood specimens will be collected from infants at delivery (cord blood), 6 and 12 months postpartum. Laboratory testing will be completed to assess levels of fasting glucose, insulin, leptin, adiponectin, lipids panels, and c-reactive protein in infants. In all cases, higher levels indicate poorer metabolic health. Analyses will be conducted to determine whether between group differences in metabolic health at delivery and over time (delivery to 12 months postpartum) are moderated or mediated by sociodemographic, biological, and psychosocial characteristics of mothers at baseline.

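### Infant metabolic status at delivery is a post-randomisation variable, so it is not a randomisation-protected moderator, and maternal traits fixed at baseline cannot be mediators

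*Protocol article*

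**What the plan says.** All references are to the protocol article.

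- **Timing.** Under Recruitment, mothers "are less than 32 weeks gestation at consent". Under Randomization, "Randomization is completed after the completion of the baseline assessment". Under Lesson frequency and duration (intervention arm), the programme is "36 comprehensive lessons delivered bi-weekly from 28 weeks gestation until birth", with further lessons after birth.
- **Delivery status as moderator.** Secondary aims analysis – Biologic measures plans a 12-month analysis of "whether the impact of the intervention on behavioral or physiologic outcomes was moderated by infant metabolic health at delivery", with a product term between study group and each biomarker in separate models. Earlier in that section, on the predictive models, it states: "All models will be controlled for study group (intervention begins before delivery".
- **Delivery status as outcome.** Secondary outcomes lists "Group differences in infant metabolic health at delivery, 6 and 12 months postpartum". The intervention section puts both roles into one exploratory aim: whether biologic factors moderate the intervention's impact, and whether the intervention can change the infant ones.
- **Baseline traits as mediators.** Secondary outcomes also asks whether between-group differences in infant metabolic health "are moderated or mediated by sociodemographic, biological, and psychosocial characteristics of mothers at baseline". Its biological examples are pre-pregnancy BMI, gestational weight gain and gestational diabetes.

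**The concern.** A moderator analysis asks whether the treatment effect differs between kinds of participant. Randomisation supports the answer only if the kind was settled before allocation, because only then are the arms comparable within each level. If treatment can move infants between levels of the delivery biomarker, the intervention and control infants found at the same level differ in other causes of that biomarker. Those causes may also drive the 12-month outcome. Having study group in the model does not repair this: it is already there, and conditioning on the biomarker is what creates the imbalance.

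Mediation has the opposite requirement, since a mediator must be something allocation can change. A trait fixed at baseline fails that by design. A list that puts pre-pregnancy BMI and gestational weight gain under one baseline label does not show which variables can play which role.

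At stake is the interpretation of declared secondary questions: a non-randomised contrast could be reported as effect modification, and a mediation question with no possible answer could be analysed.

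**Working it through.** **1. Timeline.** Assume birth at 40 weeks.
- Lessons every two weeks from 28 weeks: (40 − 28)/2 = 6 lessons before delivery, 6/36 = 17% of the programme.
- Starting at 32 weeks: (40 − 32)/2 = 4 lessons, 4/36 = 11%. It is fewer if randomisation lags consent or birth is early.

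The delivery sample follows allocation and normally follows some treatment. This agrees with the article's own parenthesis and with its listing of delivery biomarkers as an outcome.

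**2. What conditioning can do: continuous biomarker.** The documents give no effect at delivery, so every input in steps 2 and 3 is an assumption. Let M = δT + aU + e be the delivery biomarker and Y = bU + ε the later outcome. T is group, U an unmeasured shared cause with variance 1, and treatment has no effect on Y. Within an arm, the slope of Y on M is ab/(a² + σ²), where σ² is the variance of e. The group coefficient given M is −δ × slope.

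With a = b = 0.5:
- σ² = 0.75: slope = 0.25/1.00 = 0.25. σ² = 1: slope = 0.25/1.25 = 0.20.
- δ = 0: group coefficient 0.
- δ = 0.1 to 0.2: from 0.1 × 0.20 = 0.02 to 0.2 × 0.25 = 0.05 SD in size.
- δ = 0.38: 0.38 × 0.25 = 0.095, or 0.38 × 0.20 = 0.076. The 0.38 is only an upper illustration. It is the article's detectable difference at **12 months**, reproduced as (1.960 + 0.842) × √(2/109.2) = 0.379, with 260 × 0.84/2 = 109.2 per arm.
- **Interaction:** the slope is the same in both arms, so the product term, which is what the plan tests, is 0 for every δ.

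A false product term needs more. Suppose treatment also halves the link between U and M (a = 0.25 in the intervention arm). The intervention-arm slope becomes 0.125/0.8125 = 0.154 (σ² = 0.75) or 0.125/1.0625 = 0.118 (σ² = 1). The interaction is then 0.154 − 0.250 = −0.096 or 0.118 − 0.200 = −0.082. Nothing in the article supports that extra assumption.

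**3. Split biomarker.** The article also plans yes/no classifications (insulin resistant, leptin insensitive). A simulation of 2,000,000 draws had no effect on Y, within-arm correlation 0.3 or 0.5 between M and Y through U, and treatment lowering M. It compared the top quarter of M with the rest:

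| Shift in M (SD) | False contrast, high | False contrast, low | Difference |
|---|---|---|---|
| 0 | 0.00 | 0.00 | 0.00 |
| 0.1 | 0.02–0.04 | 0.02 | 0.01–0.02 |
| 0.2 | 0.05–0.07 | 0.03–0.05 | 0.03 |
| 0.38 | 0.09–0.14 | 0.06–0.09 | 0.03–0.06 |

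**4. Mediation.** An indirect effect is (allocation → mediator) × (mediator → outcome). For a trait fixed before allocation the first factor is 0 by randomisation, so the product is 0 whatever the second factor is. A nonzero sample value reflects chance imbalance. Pre-pregnancy BMI is such a trait. Gestational weight gain and gestational diabetes are not cleanly so: with entry before 32 weeks, both can develop after allocation. Table 1 also places nutrition and physical activity content in the prenatal lessons, though it does not name weight gain.

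**The case against.** The strongest reply has three parts.

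- **The analysis is exploratory and the authors know the timing.** The aim is worded as exploration, no confirmatory claim is attached to the interaction, and the parenthesis shows awareness that treatment precedes delivery. This stands and limits the severity. It does not settle the label: the sentence still asks whether impact was moderated. The hypothesis-generating caveat in the sample size section follows the psychosocial, food/water and activity moderators and does not clearly cover biomarkers.
- **The bias may be nil.** After four to six lessons, delivery status may not have moved. That is true, but the trial poses it as an open question, so the plan cannot assume it.
- **Mediation is loose wording.** No mediation model appears in the analysis section, and testing baseline traits as moderators is valid. Both stand. What fails is the word *mediated* for traits fixed before allocation, and the baseline label on variables that can develop later.

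Two stronger readings are tempting. A reader might infer that the planned test should be expected to show a false moderation of about 0.10 SD. The documents do not support that: the figure is the group coefficient at an assumed 0.38 SD delivery shift, while the interaction in the same model is zero.

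A reader might also extend the point to the completer analysis "on subjects receiving minimum intervention dose (> 50% of lessons", since attendance too is observed after randomisation. That analysis is a separate supplement to intent-to-treat, and how the threshold applies to the eight control lessons is detail an article may leave to the full protocol. Replacing it with an instrumental-variable analysis would be a trade-off, not a correction, because it assumes that allocation acts only through lessons.

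**Conclusion.** The point holds on timing and labelling. Infant metabolic health at delivery comes after allocation and is one of the trial's own outcomes, so its interaction with group is an observational association and not effect modification backed by randomisation. Mediation by traits truly fixed at baseline is impossible, and two of the three biological examples need dating against randomisation.

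No numerical size can be drawn from the documents. The illustrations rest on an assumed shift in the delivery biomarker and an assumed unmeasured shared cause. They suggest small distortions, a few hundredths of an SD for modest shifts, and none if treatment leaves delivery status unchanged. The consequence is mainly interpretive and confined to secondary analyses. The intent-to-treat primary comparisons and the use of genuine baseline traits as moderators are unaffected.

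**What to change.** 1. Base effect-modification claims on variables fixed before randomisation, such as pre-pregnancy BMI, maternal baseline measures and the stratification factors (age, site, food and water security).
2. Treat infant biomarkers at delivery as outcomes or candidate mediators. If the interaction with group is kept, label it a descriptive, non-randomised association.
3. In the secondary outcomes, delete *mediated* for true baseline characteristics and keep *moderated*.
4. Classify gestational weight gain and gestational diabetes by timing relative to randomisation. Values settled before allocation may serve as moderators, and later values only as candidate mediators.

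The cost is analysis wording only, provided those two variables can be dated from the planned chart reviews. The downside is that the delivery-biomarker question loses its causal moderation reading. Calling the biomarkers candidate mediators does not restore it, because the link from mediator to outcome is still not randomised and needs its own confounding assumptions.
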